#### Intervention arm

Patients assigned to the intervention arm will receive the healthy lifestyle informative material and a behavioral counselling on physical activity and diet by a trained physician. The healthy lifestyle informative material will be given to the patients during the behavioral counseling and discussed.

A structured exercise program of 18 months, with alternating three-month periods of supervised and non-supervised training (i.e., discontinued supervision), will be implemented. Participants will train three times per week, with at least 48 h between each exercise session.

During the 3 three-month periods of supervised training (period 1: 1st to 3rd month; period 3: 7th to 9th month; period 5: 13th to 15th month), patients will exercise at a fitness center under the supervision of an exercise specialist, who will use the WBA to constantly monitor and update the exercise prescription. In the non-supervised training periods (period 2: 4th to 6th month; period 4: 10th to 12th month; period 6: 16th to 18th month) participants will train on their own and use the WBA to access their aerobic training schedule and parameters (duration and intensity). They will also be asked to enter the actual workout performed into the WBA at the end of each self-monitored exercise session.

The aerobic exercise training protocol will be designed according to the internationally accepted recommendations and guidelines on health-enhancing PA for older adults [28–30] and T2D patients [31–34].

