#### Supervised exercise

Aerobic exercise intensity and duration will gradually increase throughout each three-month period (see Table 1).

**Table 1 Tab1:** Supervised aerobic training rate of progression for exercise session intensity and duration parameters

	Period 1	Period 3	Period 5
Intensity (%HRR range)	40–50	45–55	50–60
Duration (minute range)	20–30	30–40	40–50

Notes: Values are indicative and will be modified according to patient’s response to exercise; %HRR, heart rate reserve percentage

At the end of each session, the exercise specialist will prescribe the exercise duration and intensity of the next session, aiming for a progression rate that will allow patients to reach the upper limit range of each three-month period at least one week before its end. The WBA will help the exercise specialist to implement the progression rate by highlighting: 1) when the patient has completed two consecutive training sessions; 2) the duration and intensity of the previous sessions; 3) the pattern of the previous increases in duration and intensity (in order to alternate the type of increment); 4) the type of exercise (e.g. treadmill, bike, etc.) performed in the previous sessions (which will also be alternated).

The *10-point category ratio scale* (CR-10) of perceived exertion [38] will also be also used to monitor exercise intensity. In order to familiarize participants with the scale, the exercise specialist will 1) provide them with standardized instructions on how to use it, and 2) anchor the upper limit of the scale to a specific feeling experienced in the past during intense PA sessions (i.e., anchoring memory procedure).

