### Statistical methods

#### Sample size calculations

The sample size has been calculated to test the hypothesis of no difference in sitting time per day between intervention and control arms at the 12-month time-point (2-sided independent sample t-test; statistical power 0.8; α level of significance 0.05; 1:1 ratio between intervention and control arm). Given an expected mean value of sitting time of 500 ± 200 min per day [39, 41–43], a sample size of 112 participants in each arm will be necessary to detect a difference of 75 min per day of mean sitting times between intervention and control arm. Therefore, it was assumed that a sample size of 300 participants, i.e. 120 in each arm accounting for an expected drop-out rate of 20%, is appropriate to obtain the desired statistical power.

Sample size was computed using STATA statistical software (StataCorp).

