#### Data analyses

*Intention to treat* analysis will be adopted to account for possible issues related to noncompliance and missing outcomes. Data quality and internal consistency will be assessed *ex-post* using Cronbach’s alpha. In addition, automatic routines will be performed on the data to detect possible outliers, which will be excluded from further analyses. Explorative univariate and bivariate data analyses will then be performed.

For each study outcome, the intervention and control arm will be compared, as the difference between baseline and 12-month time-point, using independent sample t-tests. A mixed-design ANOVA will be used to compare each study outcome between intervention and control arm at the four different time-points, followed by *post-hoc* pairwise comparisons when a significant interaction is found. Participants’ characteristics (e.g., age, sex, fitness status, physical activity level, and metabolic profile) will be used as covariates, and appropriate interaction terms will be assessed and may be included in the model. For all tests, 2-sided *p* values with an α level of significance of 0.05 will be used. Bonferroni’s criterion will be used to adjust the overall α level to correct for multiple tests.

The assumptions of each statistical test will be assessed before analyses and, if not met, either data transformation will be performed or alternative statistical methods will be adopted (e.g., GEE, mixed-models, non-parametric analyses, etc.) will be performed. The residuals and goodness of fit of the models will also be examined.

SPSS Statistics (IBM) and R (R Core Team) software will be used to perform data analyses.

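### The 12-month t-test and the sample size make no allowance for clustering of intervention patients by exercise specialist or facility; the size of the effect depends on figures the protocol does not give

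*Protocol article*

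**What the plan says.** **Delivery.** Under Design, the exercise programme takes place in third-party fitness facilities. Under Intervention arm, in the supervised periods "patients will exercise at a fitness center under the supervision of an exercise specialist". Two of these periods, months 1 to 3 and 7 to 9, fall before the 12-month assessment. Under Supervised exercise, after every session "the exercise specialist will prescribe the exercise duration and intensity of the next session", and the note to Table 1 makes the tabulated ranges indicative. Under Control arm, controls receive the informative material and physician counselling, which the intervention arm also receives. They have no specialist and no facility.

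**Sample size** (Sample size calculations). The stated basis is "2-sided independent sample t-test; statistical power 0.8; α level of significance 0.05; 1:1 ratio between intervention and control arm". The inputs are "Given an expected mean value of sitting time of 500 ± 200 min per day" and a target "to detect a difference of 75 min per day of mean sitting times", from which "a sample size of 112 participants in each arm will be necessary". Randomising 300 is expected to leave 120 per arm after 20% drop-out. No design effect or ICC appears.

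**Analysis** (Data analyses). The 12-month comparison is made "as the difference between baseline and 12-month time-point, using independent sample t-tests". The mixed-design ANOVA repeats over time, and its example covariates are patient characteristics. GEE and mixed models are named as alternatives if test assumptions are not met, without naming a cluster. No specialist, facility or centre term is mentioned.

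**The concern.** Patients who share a specialist or a facility share whatever is good or poor about its delivery, so their outcomes may be correlated. Controls have no counterpart, so the clustering is in one arm only (a partially nested design). An independent-sample t-test treats the 120 intervention patients as 120 separate pieces of information.

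This is a different issue from centre. Centre is common to both arms, whereas specialist or facility clustering adds variance to the intervention mean alone. If it is present and ignored, the interval for the 12-month difference is too narrow, and a difference that owes much to a few specialists may be read as an effect of the referral scheme in general. The Discussion points to that wider reading, since it hopes such schemes will enter routine care.

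**Working it through.** **Inputs from the protocol** (Sample size calculations): difference 75 min/day, SD 200 min/day, two-sided alpha 0.05, power 0.80, 120 analysed per arm.

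**Assumed, because the protocol gives neither:** k clusters (specialists or facilities) of equal size in the intervention arm, with k = 4, 10 or 20; ICC = 0.01, 0.02 or 0.05; each patient belongs to one cluster.

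**Step 1: the plan's own figure.** n per arm = 2 × [(1.960 + 0.842) × 200/75]² = 111.6, rounded up to 112, as stated. With 300 × 0.8 / 2 = 120 per arm, the naive standard error (SE) is 200 × √(2/120) = 25.82 and power is Φ(75/25.82 − 1.960) = 0.83. Under independence the calculation is sound and has a small margin.

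**Step 2: one-arm clustering.** With m = 120/k patients per cluster:
- design effect in the intervention arm: DE = 1 + (m − 1) × ICC
- true SE = 200 × √[(1 + DE)/120]
- true SE / naive SE = √[(1 + DE)/2]
- type I error of the naive test = 2 × [1 − Φ(1.960 / ratio)]
- power with the corrected SE (normal approximation) = Φ(75 / true SE − 1.960)

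Worked case, k = 10, ICC 0.02: m = 12, DE = 1 + 11 × 0.02 = 1.22, true SE = 200 × √(2.22/120) = 27.20, ratio 1.054, type I error 0.063, power 0.79.

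| k | ICC | DE | SE ratio | Type I error | Power |
|---|---|---|---|---|---|
| 20 | 0.01 | 1.05 | 1.012 | 0.053 | 0.82 |
| 20 | 0.02 | 1.10 | 1.025 | 0.056 | 0.81 |
| 20 | 0.05 | 1.25 | 1.061 | 0.065 | 0.78 |
| 10 | 0.01 | 1.11 | 1.027 | 0.056 | 0.81 |
| 10 | 0.02 | 1.22 | 1.054 | 0.063 | 0.79 |
| 10 | 0.05 | 1.55 | 1.129 | 0.083 | 0.73 |
| 4 | 0.01 | 1.29 | 1.070 | 0.067 | 0.78 |
| 4 | 0.02 | 1.58 | 1.136 | 0.084 | 0.73 |
| 4 | 0.05 | 2.45 | 1.313 | 0.136 | 0.60 |

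Simulation of the naive t-test (20,000 trials per cell) agrees: 0.137 for k = 4, ICC 0.05; 0.081 for k = 10, ICC 0.05; 0.060 for k = 10, ICC 0.02. The SE ratio and type I error do not depend on the SD; the power figures use the protocol's 200.

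**Step 3: how much the margin absorbs.** Power stays at 0.80 or above while DE ≤ 120 × [0.375/(1.960 + 0.842)]² − 1 = 1.15. That ICC limit, 0.15/(m − 1), is about 0.005 for k = 4, 0.014 for k = 10 and 0.030 for k = 20.

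**Step 4: small-sample degrees of freedom.** With few clusters the normal approximation flatters the adjusted analysis. Satterthwaite df = (DE + 1)² / [DE²/(k − 1) + 1/119]. For k = 4 this gives about 9, 8 and 6 at ICC 0.01, 0.02 and 0.05, and noncentral-t power of about 0.68, 0.61 and 0.46.

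**The case against.** **The ICC may be close to zero.** Progression follows tabulated ranges with prompts from the web application, investigators set the parameter limits, and specialists are trained to a common protocol. The outcome is sitting time recalled at interview, not exercise performance. The 12-month visit follows three unsupervised months, and group sessions are not described. All of this stands as a reason to expect a low ICC. It does not make the ICC zero: the level reached under the specialist is the reference for the unsupervised block that follows.

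**Data analyses already allows GEE or mixed models.** This is a partial answer. Independence is an assumption of the t-test, so the clause could be used for this purpose. It is conditional, however, names no cluster, and routine checks of normality and variance would not reveal shared specialists.

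**Stronger readings that the protocol does not support.** A reader might infer that the false-positive rate certainly exceeds 5%. It does so only if specialist or facility effects vary around a mean of zero and those used are treated as a sample of a wider set. If the programme changes nothing for anyone, differences in its delivery add no variance. A reader might also infer that each patient keeps one specialist, or that the web application stores the specialist's identity with each session. The protocol says neither. If patients rotate between specialists, the simple nested design effect above does not apply as it stands; nesting by facility is less exposed to this.

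**Conclusion.** The point holds conditionally. The one-arm structure is plain in the protocol, and both the sample size and the 12-month test ignore it. If outcomes vary between specialists or facilities, and inference is to reach beyond those used, the standard error is too small and the 80% power is overstated.

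The direction is clear for any positive ICC; the size cannot be fixed from the document. With about 20 clusters and an ICC of 0.01 it is negligible, and the margin between 112 and 120 per arm absorbs it. With 4 clusters and an ICC of 0.05 it is serious. At ICC 0 the stated figures stand. The grounds support an additional analysis and a restated power, not a claim that the planned test is invalid whatever the number of clusters.

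**What to change.** - **Data collection.** Record the facility and the main supervising specialist for each intervention patient during the trial, since later reconstruction may be unreliable.
- **Data analyses.** Report the 12-month difference also from a partially nested linear mixed model: a random intercept for facility or main specialist in the intervention arm only, each control as a cluster of one, arm-specific residual variance, and Satterthwaite or Kenward-Roger degrees of freedom. If clusters are too few to estimate the variance, report instead the interval with its standard error inflated over a stated ICC range.
- **Sample size calculations.** Restate the power over that ICC range and the planned number of clusters.

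**Cost.** One or two extra identifiers and some added text. Intervals widen and stated power falls, substantially when clusters are few, as the k = 4 Satterthwaite figures show. That is why the model is proposed alongside the t-test and not as its automatic replacement. If patients rotate between specialists, a multiple-membership structure, or clustering by facility, is needed.

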**Methods:**

A randomized controlled design will be used, and an ERS, supported by a WBA, will be implemented. 300 physically inactive T2D patients (aged 65–74 years) will be assigned to either an intervention or control arm. Control arm patients will only receive behavioral counseling on physical activity and diet, while intervention arm patients will also undergo an 18-month (3 day/week), discontinuously supervised aerobic exercise training program. The trial will be divided into six three-month periods: during first, third and fifth period, an exercise specialist will supervise the training sessions and, using the WBA, prescribe exercise progression and monitor exercise adherence. Patients will exercise on their own in the other periods.

Patients’ sedentary behaviors (primary outcome), PA level, fitness status, metabolic profile, psychological well-being, quality of life, and use of health care services (secondary outcomes) will be assessed at baseline and at 6, 12, and 18 months from baseline.

Repeated measure ANCOVAs will be used to compare the intervention and control arm with respect to each study outcome measure.

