### Enrollment and arm assignment

A total of 300 older T2D patients will be enrolled and randomly assigned to either the control or the intervention arm with a 1:1 ratio, using a computerized permuted blocks randomization. The randomizations will be performed using a code created by the statisticians of the INRCA Biostatistical Center, who will not be involved in any other part of the trial. Allocation concealment will be assured because the trial staff will not know the randomization code and procedures (e.g., block sizes), and the allocation will be made only after the termination of all baseline tests (see Fig. 1).

Due to the obvious differences between the interventions (see below), neither staff nor participants will be blinded to group allocation. However, before data analysis, patient allocations and identification numbers will be replaced by categorical variables whose meaning will be unknown to data analysts.

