### Assessments/outcomes

Patients’ anthropometrics, sedentary habits, PA level, fitness status, metabolic profile, psychological well-being, quality of life, and use of health-care resources will be assessed, along with other routine assessments, on four separate occasions: at baseline and at 6, 12, and 18 months from baseline (see Table 3). The difference between the intervention and control arms at the 12-month time-point will be considered the main outcome for each measure.

**Table 3 Tab3:** Timing of study assessments

	Screening	Visit 1 baseline	Visit 2 follow-up 1	Visit 3 follow-up 2	Visit 4 follow-up 3
Weeks from randomization	-2	0	24	48	76
Visit window in weeks	–	+ 2	+/− 2	+/− 2	+/− 2
Informed consent	X				
Demographics	X				
Inclusion/exclusion criteria	X	X			
Anthropometric measures		X	X	X	X
Clinical variables		X	X	X	X
Randomization		X			
Lifestyle counseling		X			
Lifestyle informative material		X			
WBA training (only for intervention group)		X			
Blood pressure		X	X	X	X
Registration of laboratory assays		X	X	X	X
LDCW		X	X	X	X
IPAQ (short form)		X	X	X	X
EQ-5D-5L		X			X
PSQI		X			X
Healthcare resource consumption		X	X	X	X
Events					
Adverse events including hypoglycemia		X	X	X	X
New diagnoses		X	X	X	X
Intervention compliance check			X	X	X
Trial completion					X

Notes: *LDCW* long distance corridor walk, *IPAQ* International Physical Activity Questionnaire, *EQ-5D-5L* Euro Quality of Life 5 Dimensional questionnaire, *PSQI* Pittsburgh Sleep Quality Index

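### Keeping the pre-allocation baseline as one of four response levels makes the arm-by-time test that gates the visit comparisons less powerful than a baseline-adjusted test of the follow-up visits

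*Protocol article*

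**What the plan says.** All in the protocol article:

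- **Visits** (Assessments/outcomes): outcomes are measured "at baseline and at 6, 12, and 18 months from baseline". Table 3 omits the two intermediate visits for EQ-5D-5L and PSQI.
- **Allocation** (Enrollment and arm assignment): "the allocation will be made only after the termination of all baseline tests".
- **Longitudinal model** (Data analyses): "A mixed-design ANOVA will be used to compare each study outcome between intervention and control arm at the four different time-points". Post-hoc work is conditional: "pairwise comparisons when a significant interaction is found".
- **Abstract, Methods:** "Repeated measure ANCOVAs will be used to compare the intervention and control arm with respect to each study outcome measure". It names neither the levels of time nor the model term to be read.
- **Main comparison:** "The difference between the intervention and control arms at the 12-month time-point will be considered the main outcome for each measure" (Assessments/outcomes). In Data analyses the arms "will be compared, as the difference between baseline and 12-month time-point, using independent sample t-tests".

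**The concern.** Randomisation makes the expected arm difference at baseline zero. A baseline value can serve as a covariate that removes between-patient variation, or as a response level that must itself be compared between arms. The plan fixes the second use. The interaction then measures follow-up against an observed baseline difference that is pure noise. It does not use the knowledge that the true baseline difference is zero.

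What is at stake is the gate. If the interaction is not significant, the plan as worded gives no visit-specific pairwise comparisons for that outcome. A less powerful gate loses those results more often, although the data for a sharper one are already collected.

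**Working it through.** **Inputs from the protocol article (Sample size calculations):** SD s = 200 min/day, difference 75 min/day, two-sided test, "α level of significance 0.05", power 0.8, 300 enrolled, 20% drop-out.

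**Assumptions, because the article gives none:** equal correlation r between all pairs of visits (0.3, 0.5, 0.7); two effect profiles at 6, 12 and 18 months (75/75/75 and 25/50/75 min/day); complete data on the evaluable patients; no Bonferroni reduction of α.

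**1. The plan's own figure.** n = 2 × (1.960 + 0.842)² × 200² / 75² = 111.6, so 112 per arm, as stated. The exact t calculation gives 113, which is no material difference. Evaluable patients: 300 × 0.8 / 2 = 120 per arm, used below.

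**2. Bias check.** For a constant effect of 75:

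- 12-month difference minus baseline difference: 75 − 0 = 75.
- Arm main effect averaged over four visits: (0 + 75 + 75 + 75)/4 = 56.25, which is 3/4 of 75.

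A simulation (4,000 runs, 120 per arm, r = 0.6) gave 75.0 for the first, 74.8 for the raw 12-month difference and 56.2 for the four-visit main effect. The 3/4 ratio holds for any profile: 25/50/75 gives 150/4 = 37.5 against a follow-up mean of 50.

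**3. Power.** Let Σd² be the sum of the squared follow-up differences and (Σd)² the square of their sum. Both tests have 3 numerator df. Their noncentrality parameters are:

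- Four-level interaction: (n/2) × [Σd² − (Σd)²/4] / [s²(1 − r)].
- Three follow-up differences adjusted for baseline, with per-patient covariance s²[(1 − r)I + r(1 − r)J], where I is the identity matrix and J the matrix of ones: (n/2) × [Σd² − (Σd)² × r/(1 + 3r)] / [s²(1 − r)].

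Since r/(1 + 3r) is below 1/4 for every r below 1, the second is larger unless the differences sum to zero. The two converge as r approaches 1.

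Worked case, constant 75 and r = 0.3: Σd² = 16,875 and (Σd)² = 50,625.

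- Interaction: 60 × (16,875 − 12,656.25) / 28,000 = 9.04.
- Adjusted: 60 × (16,875 − 50,625 × 0.1579) / 28,000 = 19.03.

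For 25/50/75, Σd² = 8,750 and (Σd)² = 22,500. Power from the noncentral F:

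| Profile | r | Noncentrality: interaction / adjusted | Power: interaction | Power: adjusted |
|---|---|---|---|---|
| 75/75/75 | 0.3 | 9.04 / 19.03 | 71% | 97% |
| 75/75/75 | 0.5 | 12.66 / 20.25 | 86% | 98% |
| 75/75/75 | 0.7 | 21.09 / 27.22 | 98% | 99.6% |
| 25/50/75 | 0.3 | 6.70 / 11.14 | 57% | 80% |
| 25/50/75 | 0.5 | 9.38 / 12.75 | 73% | 86% |
| 25/50/75 | 0.7 | 15.62 / 18.35 | 93% | 96% |

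The choice of denominator df for the adjusted test moves its power by about half a percentage point at most.

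**The case against.** A four-level arm-by-time ANOVA read through its interaction is a standard, unbiased analysis, and the degree of freedom that contrasts follow-up with baseline is not wasted. For a constant effect it carries all of the interaction signal. This stands.

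The main outcome does not depend on this model either. It is the 12-month difference, tested by a separate t-test on change. The article also lists covariates, allows mixed models if assumptions fail, and may leave covariate coding to an analysis plan. This stands in part. Exact coding can be deferred, but the article itself fixes four response levels and an interaction gate, and it does not list the outcome's own baseline among its example covariates.

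A reader might infer more: that the trial's treatment effect will be understated by one quarter, because the arm term averages in a visit with no effect. The arithmetic for that term is right, but the documents do not support the conclusion. Data analyses acts on the interaction, the abstract names no term, and nowhere is the four-visit arm main effect given as the estimate or test of effect.

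Finally, the gain depends on assumed correlations and is small when they are high.

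**Conclusion.** The point holds as one of efficiency. Nothing the plan commits to is biased by this choice. On the assumptions shown, using baseline as a response level costs the gating test about 26, 12 and 2 percentage points of power at r = 0.3, 0.5 and 0.7 for a constant 75 min/day (97 − 71, 98 − 86, 99.6 − 98). For 25/50/75 the loss is about 23, 13 and 3 points. At r = 0.3 with the design effect at every follow-up, the gate misses about 29% of the time instead of about 3%. The adjusted test was ahead at every correlation tried for both profiles. The absolute powers would be lower under a Bonferroni-adjusted α. This is a free improvement rather than something wrong as written.

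**What to change.** In Data analyses, and consistently in the abstract:

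- Model the 6-, 12- and 18-month values as the repeated responses.
- Enter the same outcome's baseline value as a covariate with its own slope at each visit. Alternatively, keep baseline in the model with the arm means constrained to be equal there.
- Replace the four-level interaction gate with a joint 3-df test of the three follow-up arm differences.
- Read the arm differences at 6, 12 and 18 months from this model.
- State that an arm main effect averaged over all four visits will not be used as the treatment effect.

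The cost is a short change of wording. Baseline is already collected, no visit or patient is added, and the SPSS and R software already named can fit the model.

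### Single-step Bonferroni is the stated multiplicity correction; Holm's step-down procedure over the same tests gives the same familywise control and never fewer rejections

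*Protocol article*

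**What the plan says.** The Data analyses section sets out three layers of testing. First, a t-test per outcome: "For each study outcome, the intervention and control arm will be compared, as the difference between baseline and 12-month time-point, using independent sample t-tests". Second, a mixed-design ANOVA over the four time-points. Third, further comparisons, "followed by *post-hoc* pairwise comparisons when a significant interaction is found". It then gives the error rate, "For all tests, 2-sided *p* values with an α level of significance of 0.05 will be used", and directly after that the correction: "Bonferroni’s criterion will be used to adjust the overall α level to correct for multiple tests". No list of tests, number of tests or adjusted threshold is given.

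The secondary domains in the abstract are "PA level, fitness status, metabolic profile, psychological well-being, quality of life, and use of health care services (secondary outcomes"). Under Assessments/outcomes, "The difference between the intervention and control arms at the 12-month time-point will be considered the main outcome for each measure". The sample size section sizes only sitting time ("2-sided independent sample t-test; statistical power 0.8; α level of significance 0.05; 1:1 ratio between intervention and control arm"); no secondary outcome is powered.

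**The concern.** The secondary objectives describe several benefits of one 18-month training programme: activity, fitness, metabolic profile, well-being, quality of life and health-care use. If the programme works, several of these should move together. Single-step Bonferroni holds each test to 0.05/m however many of the other tests are clearly positive, and it loses most against a step-down method in exactly that situation. Real secondary effects could then be reported as non-significant although the same data would support them at the same familywise error rate. Because these outcomes were not powered to begin with, an avoidable loss is worth removing.

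**Working it through.** **1. The plan's own figure.** Inputs from the sample size section: "expected mean value of sitting time of 500 ± 200 min per day", difference 75, two-sided 0.05, power 0.80.

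n per arm = 2 × (1.960 + 0.842)² × (200/75)² = 2 × 7.849 × 7.111 = 111.6, so 112. This agrees with the protocol. With 20% drop-out, 150 × 0.8 = 120 per arm. The calculation uses an unadjusted 0.05 and concerns the primary outcome only, so the present point leaves it untouched.

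**2. Why Holm never rejects less.** Order the m p values. Bonferroni compares each with 0.05/m. Holm compares the smallest with 0.05/m, the next with 0.05/(m − 1), and so on, stopping at the first failure. Every Holm threshold is at least 0.05/m, so whatever Bonferroni rejects, Holm rejects.

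**3. Why the error control is the same.** Let m₀ of the hypotheses be true nulls. When Holm first rejects a true null, at most m − m₀ rejections have come before it, so the threshold at that step is at most 0.05/m₀. A false rejection therefore requires the smallest of the m₀ null p values to be at or below 0.05/m₀. That has probability at most m₀ × 0.05/m₀ = 0.05, with no assumption about dependence.

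**4. How large the family might be (assumption).** The Secondary outcome measures section, read through to Anthropometry, yields about ten measures: MET per week, VO₂max, EQ-5D-5L score, its visual scale, health-care cost, fasting glucose, HbA1c, PSQI, BMI and waist-to-hip ratio. Table 3 schedules EQ-5D-5L and PSQI only at baseline and Visit 4, although the text above the table places quality of life at all four occasions. Without those three measures, seven remain at 12 months. Both sizes are shown.

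**5. Power.** Assumptions: correlation 0.3 between test statistics, and 80% power per affected outcome at unadjusted 0.05, so noncentrality δ = 1.960 + 0.842 = 2.802. Bonferroni power is Φ(δ − z), where z is the two-sided critical value at 0.05/m:

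- m = 10: z = 2.807, Φ(−0.005) = 0.498
- m = 7: z = 2.690, Φ(0.111) = 0.544

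Holm power comes from simulation, as average power per affected outcome:

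| Outcomes | Affected | Bonferroni | Holm |
|---|---|---|---|
| 10 | 10 | 50% | 61% |
| 10 | 5 | 50% | 53% |
| 10 | 3 | 50% | 51% |
| 7 | 7 | 54% | 66% |
| 7 | 4 | 54% | 58% |
| 7 | 1 | 54% | 54% |

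With 90% unadjusted power and all 10 affected, the figures are 67% and 79%. With 5 true nulls among 10 (80% power), simulated familywise error is 2.4% for Bonferroni and 3.4% for Holm, both under 5%. No simulated trial had a Bonferroni rejection that Holm missed. The chance of at least one rejection is identical, because both start at 0.05/m.

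**6. A second set-up.** Take 120 per arm, a standardised effect of 75/200 = 0.375 and independent outcomes. With all effects real, average power goes from 0.60 to 0.73 (m = 6) and from 0.52 to 0.63 (m = 12). With half real, it goes from 0.61 to 0.64 and from 0.52 to 0.55. With one real, the gain is at most 0.001.

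**The case against.** The strongest reply is that this is a preference between two valid procedures. Bonferroni is pre-specified, controls the familywise error under any dependence, and makes no figure in the protocol wrong. It also has simple matching simultaneous confidence intervals, which Holm does not. And the gain of 11 to 12 points is a best case: it shrinks to about 3 or 4 points when roughly half the outcomes respond and vanishes when one does. All of that stands. Holm is superior in rejections, not in every respect.

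Three stronger readings are tempting, and the document does not support them.

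- A reader might infer that the protocol fixes Bonferroni specifically across the secondary outcomes at about 0.005 each. It names neither a family nor a threshold. The sentence follows t-tests on every outcome, the ANOVA and the post-hoc comparisons, and could cover any of these. Ten is also not a settled count, given Table 3.
- A reader might infer that the primary comparison falls inside the family and is therefore underpowered. If it did, power at 120 per arm would fall from 0.83 to 0.75 with two tests or 0.61 with six. But the text does not put it there, the sample size uses an unadjusted 0.05, and changing to Holm would not settle that question.
- A reader might conclude that the correction should be confined to the 12-month secondary comparisons. That would leave uncorrected other tests that the present wording can cover, such as the 18-month EQ-5D-5L and PSQI comparisons and the post-hoc pairwise tests.

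**Conclusion.** The point holds as an optional improvement. For any family the authors had in mind, Holm at familywise 0.05 keeps the error guarantee that Bonferroni gives and can only add rejections. Steps 2 and 3 establish this without assumptions. The size does rest on assumptions that the protocol does not supply: the number of tests, equal power across affected outcomes, a common correlation of 0.3, and above all the share of outcomes that truly respond. Across the scenarios checked, the gain in average power runs from nothing to about 13 percentage points. Bonferroni is not a mistake, and no stated result would become invalid by keeping it.

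**What to change.** In Data analyses, name the Holm step-down procedure at familywise 0.05 where Bonferroni's criterion now stands. Apply it to the same tests that the Bonferroni correction was meant to cover, including the secondary outcomes at their scheduled time-points and the post-hoc pairwise comparisons, and write that set down so that the scope is neither widened nor narrowed by the change. Report Holm-adjusted p values.

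The cost is a change of wording. R is already named as analysis software, and its p.adjust function does the calculation. The downside is that simultaneous intervals matching Holm are less simple, so unadjusted 95% confidence intervals should be shown beside the adjusted p values and labelled as unadjusted. The change should be made before the arms are compared.
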